**Annex 2. Study flow chart**

**Eligible subjects**

**(children attending ED)**

**Enrolled subjects**

**Inclusion/exclusion criteria**

Excluded if failure to meet inclusion criteria

Excluded if parental consent not given

**In case of vomiting or liquid refusal**

Excluded if ORT succeeds succeedssucceededss

**First oral rehydration solution (ORS) administration**

**Written parents consent**

**After 45-60 minutes from treatment administration  new ORT challenge**

**Oral Ondansetron**

0,15 mg/Kg of body weight

Centralised random allocation to a dose of

**Oral Domperidone**

0,5 mg/Kg of body weight

**Oral placebo**

**Outcomes evaluation**

**Outcomes evaluation**

**Outcomes evaluation**

Intention to treat analysis

Second dose given in case of vomiting within 15 minutes

Patients assessed at 30 minute intervals for a minimum of 6 hours of hospital stay. Telephone follow up at 48 hours after discharge

**Annex 3. Abbreviations**

AAP: American Academy of Pediatrics

AIFA: Agenzia Italiana del Farmaco (Italian Agency of Drugs)

AG: Acute gastroenteritis

ARNO: ARNO project (ON-LINE drug prescription monitoring system - global vision)

ED: emergency department

ESPGHAN: European Society for Paediatric Gastroenterology, Hepatology, and Nutrition

DRG: Diagnosis-related group

IRCCS: Istituto di Ricovero e Cura a Carattere Scientifico

IVT: intravenous fluid therapy

NICE: National Institute for Clinical Excellence

NNT: Number Need to Treat

ORS: oral rehydration solution

ORT: oral rehydration therapy

RCT: randomised controlled trial

WHO: World Health Organization

**No changes were made to the following sections:**

**BACKGROUND**

**OBJECTIVES**

**REFERENCES**

**Annexes**

Changes in Methods section are highlighted below:

**METHODS**

**Study Design**

The study is a prospective, multicentre, double-blind randomized controlled trial. The study will be coordinated by the Institute for Maternal and Child Health - IRCCS Burlo Garofolo (Trieste) and by the Maternal and Child Health Laboratory of the Institute Mario Negri (Milan).

**Study Population**

The study will be conducted in hospital and the recruitment setting will be the paediatric emergency departments (ED). Children between 1 to 6 years will be included in the study.

Consecutive subjects accessing the ED during a 18 months period will be evaluated for inclusion/exclusion criteria by the doctor on call. The following inclusion and exclusion criteria will be used:

Inclusion Criteria

1) age from 1 to 6 years;

2) presumptive clinical diagnosis of acute gastroenteritis in patients with vomiting, with or without diarrhoea (see Annex 1 for AG clinical diagnosis and vomiting definitions);

3) more than three episodes of non-bilious, non-bloody vomiting within the previous 24 hours;

Exclusion Criteria:

1) treatment with antiemetics or antidiarrhoic drugs in the 6 hours prior to access to ED;

2) underlying chronic diseases (eg, malignancy, gastroesophageal reflux, migraine, renal failure, hypoalbuminemia, liver disease);

3) severe dehydration defined by a standard clinical score of >18 for children 12-24 months or >16 for children >24 months of age (see Annex 1) (20);

4) known hypersensitivity to ondansetron or domperidone;

5) previous enrolment in the study

6) concomitant use of drugs that prolong the QT interval (i.e., macrolides, quinolones, ketoconazole, fluconazole, salmeterol, trimetoprim)

7) language barriers or inability to perform the telephone follow-up

**Intervention**

After checking the inclusion and exclusion criteria, administration of oral rehydration solution (ORS) will be started following a standard protocol (see Annex 1 for definition). ORS will be prescribed by the doctor on call and administered under supervision of an emergency departments nurse.

In case of failure of the initial ORS administration (vomiting after ORS or fluid refusal), patients will be randomized to receive an oral administration of:

1) ondansetron syrup (0,15 mg/Kg of body weight);

2) domperidone syrup (0,5 mg/Kg of body weight);

3) placebo.

Children vomiting within 15 minutes after receiving the drug will be given a second dose.

After 45 to 60 minutes from treatment administration, a new attempt to administer ORS will be done, according to the standard protocol (see Annex 1).

After an adequate information of the study and before random allocation of subjects, written consent will be obtained by the doctor on call from the parents or legal guardian of children fulfilling the entry criteria and failing initial ORS administration. A register of all patients who were proposed to be enrolled in the study will be kept, and reason for refusal will be recorded.

A flow chart describing comparison groups and trial procedures is added in the Annex section (Annex 2).

**Outcomes**

Primary Outcome:

Percentage of patients needing nasogastric or intravenous rehydration after symptomatic oral treatment failure, defined as vomiting or fluid refusal after the second attempt of ORT.

Secondary Outcomes:

1) Percentage of subjects needing hospital admission for the same illness;

2) Percentage of subjects needing observation stay for more than 6 hours for the same illness;

3) Total emesis duration in the 3 allocation groups;

4) Number of episodes of vomiting in the 3 treatment groups during the follow-up period;

5) Percentage of subjects presenting adverse events.

Data regarding the study outcomes will be collected by doctors on call or bedside nurse during the patient stay in the ED (or any other paediatric unit devoted to short observation) using a standardized assessment tool. Patient will be reassessed at 30 minute intervals for a minimum of 6 hours. During the patients' hospital stay, doctors and nurses will be blind to treatment assignment. A telephone follow up call will be made 48 hours after ED discharge using a standard form by a research assistant blind to treatment assignment.

Note: We discussed whether to consider hospital admission as the primary study outcome. Unfortunately, criteria for hospital admission could differ in different hospitals and ED settings and various administrative typologies of hospital admission exist in the study centres, including the “short observation” which may vary across centres in the way it is defined and applied. A recent systematic review on ondansetron confirms that when considering hospitalization as an outcome, there is great heterogeneity. Authors indicate different criteria for hospital admission as a possible explanation (15). Definition and standardization of hospital admission criteria are difficult due to differences in the administrative and organizational characteristics among participating EDs. Furthermore, nasogastric or intravenous rehydration represent a more objective outcome and represent anyway a good proxy measure of hospital admission.

**Randomization**

Patients will be randomly assigned in fixed block size of nine to receive ondansetron or domperidone or placebo. Randomisation list will be generated using STATA software and will be stratified according to participating centres. Randomization procedure will be centralized and managed by an independent statistician at the Coordinating Centre. The randomization sequence will be provided to the central pharmacy, which will prepare and dispense to participating hospitals active drugs and placebo. After checking eligibility and failure of first ORS administration, the next available bag containing drug preparations will be opened by the doctor on call or by the bedside nurse and a weigh-appropriate dose will be administered to patients. All study investigators, personnel, and participants will be unaware of the randomization procedure and pharmaceutical preparations assignments.

**Blinding**

The pharmaceutical preparation will be directly sent to participating centres in closed, opaque and consecutive numbered bags by the central pharmacy. Drug preparations will be indistinguishable by taste, odour and appearance. All study investigators, personnel, and participants will be blind to preparations administered.

**Information retrieval**

A questionnaire detailing demographic data, medical history, allergies, history of present illness, and medication received will be collected at enrolment by doctors on call. Data relative to study outcomes will be collected by doctors on call or bedside nurse during the hospital stay. Patient will be reassessed at 30 minute intervals for a minimum of 6 hours and data will be collected at each assessment. Forty-eight hours after discharge, a blind researcher assistant will telephone the child's family to evaluate, using a standard form, the gastroenteritis evolution, the possible need of hospitalisation or readmission in ED and the final outcome.

Paper records will be transferred by each centre into electronic data base.

The percentage of subjects lost to follow up, based on available literature and taking into account the short follow up period, can be estimated as less than 10% (20,22).

**Sample size estimates**

Studies comparing ondansetron versus placebo are available in the literature while it was impossible to identify studies comparing ondansetron and domperidone. Two studies evaluating domperidone versus placebo were also identified, even if characterized by low methodological quality and small sample size. Based on the available literature, it appears plausible to hypothesize that ondansetron is more efficacious in comparison to placebo or domperidone and therefore design the study as a superiority trial. For sample size estimation we specifically referred to the Roslund RCT (22) that implemented a similar protocol to ours (enrolment of subjects with clinical acute gastroenteritis who failed initial ORS administration in the ED). Taking into account the above stringent eligibility criteria, we estimate that the enrolment of 540 children (i.e. 180 patients in each arm) will provide the study with a statistical power of 80% to detect a change from 50% in placebo group to 35% in domperidone group and 20% in ondansetron group in the proportion of children requiring nasogastric or intravenous rehydration, given a two-sided type I error of 0,05. Given the lack of available efficacy estimates, domperidone efficacy was estimated as intermediate between ondansetron and placebo.

**Statistical analysis**

Baseline characteristics of the three groups will be compared by the chi-square test for proportions and the analysis of variance or Kruskal-Wallis test (depending on data distribution) for continuous variables. Relative risks and 95% confidence intervals will be presented for categorical data while means and standard deviations for continuous data. For categorical outcomes, differences between groups will be evaluated using the chi-square test; for continuous outcomes using analysis of variance or Kruskal-Wallis test, depending on data distribution. Analyses will be performed with STATA software (version 9) according to the intention-to-treat principle. All p values will be two-sided, with a p value of less than 0.05 used to indicate statistical significance.

Two interim analysis are planned, following the criteria defined by O'Brien-Fleming (Schulz KF. Lancet 2005;365:1657-61). The first interim analysis is planned at July 2013, two years after the enrolment of the first subject in the study. The interim stopping level (p value) for the difference between ondansetron vs domperidone/placebo is set at 0.0005. The second interim analysis is planned for November 4th 2013 (the official closing date of the study) if: 1) the first analysis had not achieved the necessary significance, or 2) the initially estimated sample size had not been reached. The interim stopping level (p value) for the difference between ondansetron vs domperidone/placebo is set at 0.014.

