**OBJECTIVES**

- Primary Objective: To evaluate whether the oral administration of a symptomatic drug (ondansetron or domperidone) prevents intravenous or nasogastric rehydration in children vomiting and diagnosed acute gastroenteritis.
- Secondary Objective: To assess whether the oral administration of a symptomatic drug (ondansetron or domperidone) reduces the total duration and number of vomiting episodes and the need for hospital admission or ED access.

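### The three-arm primary outcome has no stated contrast, gate or multiplicity rule for the final analysis: depending on the reading, the chi-square at 0.05 leaves the pairwise questions unanswered or carries a familywise error of about 9% to 12%.

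*Supplement*

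**What the plan says.** The rule for the primary outcome, a binary one, is in the Statistical analysis section of the final protocol: "For categorical outcomes, differences between groups will be evaluated using the chi-square test". The same sentence assigns analysis of variance or Kruskal-Wallis to continuous outcomes. Relative risks with 95% confidence intervals are to be presented, and the threshold is general: "All p values will be two-sided, with a p value of less than 0.05 used to indicate statistical significance".

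The questions the trial asks are set elsewhere. The primary objective is "To evaluate whether the oral administration of a symptomatic drug (ondansetron or domperidone) prevents intravenous or nasogastric rehydration". The Sample size section hypothesises that ondansetron is superior to placebo or domperidone. It plans "the enrolment of 540 children (i.e. 180 patients in each arm") with 80% power "to detect a change from 50% in placebo group to 35% in domperidone group and 20% in ondansetron group", "given a two-sided type I error of 0,05".

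The only contrast named in the Statistical analysis section is in the interim rule: ondansetron against domperidone/placebo, with stopping levels of 0.0005 and 0.014. It does not say whether those two arms are pooled or compared separately. No contrast is named for the final analysis.

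**The concern.** With three arms, a chi-square for differences between groups can mean one 2-df test of all three arms or a set of two-arm tests. The text does not say which, and each has a cost.

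- **Three-group test.** It is the natural reading, since analysis of variance and Kruskal-Wallis are global tests for three arms. A significant result shows only that the arms are not all alike. It does not show whether ondansetron beats domperidone or whether domperidone beats placebo.
- **Pairwise tests.** Each judged at 0.05 with no gate, they give two or three chances of a false primary claim, and the 5% error in the Sample size section no longer describes the trial.

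Because the choice is open, the set of confirmatory contrasts and the error control could be settled after the data are seen. The trial is meant to guide a choice between two drugs, so the pairwise results are what readers will use.

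**Working it through.** **Inputs.** 180 per arm; rates 50% (placebo), 35% (domperidone), 20% (ondansetron); two-sided 0.05; 80% power. All are from the Sample size section of the final protocol.

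**1. Reproducing the plan's 180 per arm.** Two proportions, pooled variance:

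n = [z(0.975)·√(2p̄(1−p̄)) + z(0.80)·√(p₁(1−p₁)+p₂(1−p₂))]² / (p₁−p₂)²

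For 50% vs 35%, p̄ = 0.425. Then n = (1.960×0.6991 + 0.8416×0.6910)² / 0.15² = 1.9518² / 0.0225 ≈ 169.3, so 170 per arm, or 183 with the continuity correction. The other pairs need 138 (151 corrected) for 35% vs 20%, and 39 (45 corrected) for 50% vs 20%. The stated 180 is within 3 of the corrected figure for 50% vs 35%.

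**2. What the 80% refers to.** The three-group test has noncentrality 180×(0.15² + 0 + 0.15²)/(0.35×0.65) = 8.1/0.2275 = 35.6 on 2 df, which gives 99.99% power. So 80% is not the power of the three-group test. It fits the hardest pair at an undivided 0.05. Formula power per pair at 180 per arm:

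- Placebo vs domperidone: Φ[(0.15×√180 − 1.3702)/0.6910] = Φ(0.929) = 82.4%.
- Domperidone vs ondansetron: Φ[(2.0125 − 1.2377)/0.6225] = Φ(1.245) = 89.3%.
- Placebo vs ondansetron: over 99.9%.

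**3. Three-group reading.** Simulated at 50/35/20% (300,000 trials), the three-group test was significant in 99.99% of trials. Yet ondansetron vs domperidone was not significant at 0.05 in about 10%. A significant global result therefore does not settle the pairwise question.

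**4. Ungated pairwise reading, all arms equal, single look.**

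| Confirmatory tests, each at 0.05 | Theory | Simulation, 180 per arm, null rate 20%, 35% or 50% |
|---|---|---|
| Both ondansetron contrasts | 9.1% (bivariate normal, correlation 0.5) | 9.2–9.3% |
| All three pairs | 12.2% (studentized range, critical value 1.96×√2) | 12.3–12.6% |

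Treating three tests as independent would give 1 − 0.95³ = 14.3%. That is too high, because the contrasts share arms. The simulations used 1,000,000 trials per null rate.

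**5. Three-group gate, then pairs at 0.05.** With three arms, any two pairwise equalities imply the third, so the only intersection hypothesis is that all arms are equal. Testing it first makes the procedure closed.

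- Global null: familywise error 4.8–5.0%.
- One arm different, two equal: 5.0–5.1%.
- Power at the planned rates (simulated): 82% domperidone vs placebo, 90% ondansetron vs domperidone, over 99.9% ondansetron vs placebo. Without the gate the figures are the same to the precision shown.

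For comparison, Bonferroni at 0.05/3 cuts domperidone vs placebo to 68.8% and would need 227 per arm for 80% (240 with continuity correction).

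**The case against.** The strongest defence is that the text, taken naturally, describes a three-group test, and that test holds 5%. Relative risks need two groups, so pairwise estimates are planned as well. A global test followed by pairwise results is, with three arms, very nearly the closed procedure recommended here. This stands as far as it goes: the plan is one sentence from being sound. But it does not make the pairwise tests conditional on the global one, and it applies 0.05 to every p value.

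Second, the plan is not silent on contrasts. The superiority hypothesis and the interim rule both centre on ondansetron. If only the two ondansetron contrasts count, the error is about 9%; if domperidone/placebo means the two arms pooled, there is one test at 5%. This also stands, and is why a range is given. The primary objective names either drug, however, so domperidone vs placebo cannot be excluded.

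Third, no separate analysis plan is shown, and testing order is often placed there. That would excuse missing detail. Here, though, the protocol states its own test and threshold, and that threshold applied to its own pairwise questions exceeds its own 5%.

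Fourth, a reader might infer that the 80% is wrong because the chance of showing both adjacent steps (50% above 35%, and 35% above 20%) is only 72%, or 46% at 0.014. The documents do not support that. Nothing makes success depend on both steps, and each single contrast exceeds 80%. For ondansetron beating both comparators, joint power at 0.05 is 89.6%. The level 0.014 is an interim stopping level, and the 46% assumes a full sample at a look that may take place because the sample has not been reached.

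**Conclusion.** The point holds. The final analysis of the primary outcome lacks a stated contrast, gate or multiplicity rule, and neither reading of the chi-square sentence both answers the pairwise questions and holds 5%.

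The size depends on the reading: 5% for the three-group test, about 9% for two ungated ondansetron contrasts, about 12% for all three pairs. A reader might take 12% as the trial's error rate and say the 5% claim is wrong by a factor of about 2.5. The documents do not support that, because they do not establish that three ungated confirmatory tests are intended. It is the top of the range.

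The error figures assume equal rates in all arms, 180 per arm and a single look. The power figures assume 50/35/20%. The contrast and levels of the interim looks are a separate matter and are not included. The 80% is not an error; it needs to be labelled as the power for one pair.

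**What to change.** In the Statistical analysis section, for the final analysis of the primary outcome, state that:

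1. the three-group chi-square is done first, at the level set for the final analysis;
2. only if it is significant are ondansetron vs placebo, ondansetron vs domperidone and domperidone vs placebo each tested by a two-group chi-square at that same level;
3. if it is not significant, the pairwise relative risks and 95% intervals are reported as descriptive.

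In the Sample size section, say that the 80% is the power for 50% vs 35%, and give the power per contrast at 180 per arm: about 82% for domperidone vs placebo, about 90% for ondansetron vs domperidone, over 99.9% for ondansetron vs placebo.

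A fixed testing sequence named in advance, each step at 0.05, would also hold 5% with the same sample size. What matters is that one rule is written down before unblinding. The cost is a few sentences: no added patients and, at the planned rates, no lost power. The interim rule need not change for this purpose.

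### Randomisation is stratified by centre but the primary chi-square is not; if rehydration rates differ between centres, the test is valid but somewhat conservative

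*Supplement*

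**What the plan says.** In the final protocol, the Randomization section states: "Patients will be randomly assigned in fixed block size of nine to receive ondansetron or domperidone or placebo". It adds: "Randomisation list will be generated using STATA software and will be stratified according to participating centres".

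The Statistical analysis section names the test: "For categorical outcomes, differences between groups will be evaluated using the chi-square test". On the effect measure it says: "Relative risks and 95% confidence intervals will be presented for categorical data". Neither sentence mentions centre, and the section describes no stratified test or adjusted model. The paragraph on the two interim analyses adds none. The Sample size estimates section does not refer to centre either.

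On differences between hospitals, the note under Outcomes says that "criteria for hospital admission could differ in different hospitals and ED settings". That remark concerns hospital admission, a secondary outcome. The same note prefers nasogastric or intravenous rehydration as the primary outcome because it is more objective, though it also calls it a good proxy for admission. No centre rates, variance or intraclass correlation are given for the primary outcome.

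**The concern.** Balancing the arms within centre removes most of the between-centre variation from the treatment comparison. The ordinary chi-square does not take account of this. Its standard error is built from the overall event rate and so still contains the variation between centres. If centres differ in how often children go on to nasogastric or intravenous fluids, that standard error is too large. P values are then conservative and confidence intervals too wide, and the test gives up power that the stratified design has already made available.

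What is at stake is precision and some power, mainly for the two contrasts with 15-point differences. There is also a smaller gain in discipline: fixing the stratified analysis in advance removes any later choice between crude and adjusted results.

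**Working it through.** **1. The plan's own figure.** The inputs from Sample size estimates are 180 per arm, 80% power, two-sided 0.05, and rates of 50% (placebo), 35% (domperidone) and 20% (ondansetron). The binding pairs are those 15 points apart, and 50% vs 35% needs the most children. With p̄ = 0.425:

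n = [1.96·√(2·0.425·0.575) + 0.8416·√(0.5·0.5 + 0.35·0.65)]² / 0.15² = (1.370 + 0.582)² / 0.0225 ≈ 170 per arm, or 183 with continuity correction.

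Power at 180 per arm is 82.4% uncorrected and 79.4% corrected. The stated 180 is therefore reproduced to within 3% by the corrected formula. For 35% vs 20%, n = 138 (151 corrected) and power is 89.3%. For 50% vs 20%, power exceeds 99.9%.

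**2. Why the crude test is conservative.** Let p_k be the event rate in centre k and p the overall rate. With exact balance within centres and no treatment effect, the ratio of the true to the assumed standard error is

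r = √[1 − Var(p_k) / (p(1 − p))],

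and the true type I error is 2·[1 − Φ(1.96 / r)]. As an example, take p = 0.5 and a between-centre SD of 0.8 on the log-odds scale. Then Var(p_k) ≈ 0.031, r = √(1 − 0.031/0.25) = 0.936, and the type I error is about 3.6%. The crude standard error is too large by a factor of 1/0.936 ≈ 1.07.

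**3. Simulation.** The inputs from the documents are 540 children, three arms, blocks of nine within centre, the three event rates and a two-sided 0.05 level. The following are assumptions:
- There are 17 centres. Unit numbering in the Summary of changes reaches 17, but the unit list is not shown.
- Centres are of unequal size.
- Centre effects are normal on the log-odds scale, with overall rates held at the protocol's values.
- The treatment effect is homogeneous on that scale.
- One pair of arms is tested at a time, because the plan does not say how the pairwise comparisons are handled.

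The crude two-arm chi-square was compared with the Cochran-Mantel-Haenszel (CMH) statistic

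z = Σ(x_k − n_0k·t_k/n_k) / √Σ[n_0k·n_1k·t_k(n_k − t_k) / (n_k²(n_k − 1))].

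Here x_k is the number of events in one arm at centre k, n_0k and n_1k are the arm sizes, n_k is their sum, and t_k is the total number of events. Small centres were not merged. There were 20,000 runs per cell for the figures below, with Monte Carlo error of about 0.15 points for type I error and 0.3 points for power.

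| Centre SD | 10th–90th percentile of centre placebo rates | Type I error at 50% = 50%, crude → CMH | Power 50% vs 35% | Power 35% vs 20% |
|---|---|---|---|---|
| 0 | 50–50% | 5.1 → 5.2% | 82.7 → 82.5% | 89.8 → 89.5% |
| 0.3 | 41–59% | 5.1 → 5.4% | 83.0 → 83.3% | 89.7 → 89.7% |
| 0.5 | 35–65% | 4.6 → 5.2% | 82.6 → 83.7% | 89.9 → 90.4% |
| 0.8 | 26–74% | 3.7 → 4.9% | 83.8 → 86.7% | 90.6 → 91.9% |
| 1.0 | 22–78% | 3.5 → 5.2% | 84.3 → 88.3% | 90.8 → 93.1% |
| 1.5 | 13–87% | 2.3 → 5.0% | 85.6 → 92.4% | 91.3 → 95.5% |

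For 50% vs 20%, power is about 100% with either test throughout. The simulated 3.7% at SD 0.8 agrees with the 3.6% from step 2.

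**The case against.** The strongest objection is that nothing in the documents shows that the primary outcome varies by centre. The remark about differing criteria concerns admission, and the same note presents rehydration as the more objective measure. The protocol also standardises much of the pathway: a common oral rehydration schedule, a common dehydration score, and a defined failure criterion of vomiting or fluid refusal after the second attempt. This stands to the extent that the loss must be stated conditionally. A reader might infer that the protocol itself admits differing rehydration rates between centres; it does not. Variation remains plausible, because starting fluids is a clinical decision and the note treats the outcome as a proxy for admission.

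A second objection is that no promised power is lost. This stands for the stated design: in every scenario the crude test keeps at least 82% power at 180 per arm and 0.05. The loss is relative to a better test. It is also smaller where the trial's main hypothesis lies, since ondansetron is compared with domperidone at 35% vs 20% and with placebo at 50% vs 20%.

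A third objection is that handling of centre is commonly left to a separate analysis plan, and none is shown. This carries less weight here, because the protocol is not silent: it names a test, and that test leaves out the stratification factor.

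A fourth is sparse strata. With 17 centres the average is 540/17 ≈ 32 children, or 10 to 11 per arm, and fewer if recruitment falls short. That supports having a merging rule, but CMH held its level at about 5% in the simulation without one.

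**Conclusion.** The mismatch between stratified allocation and unstratified analysis is clear in the text. Its cost depends on between-centre variation that the documents do not quantify. Over a log-odds SD of 0 to 1.0, the power forgone runs from nil to about 4 points for 50% vs 35%, and from nil to about 2.3 points for 35% vs 20%. The crude type I error runs from about 5.1% down to 3.5%. The 7-point gain at SD 1.5 needs centre placebo rates spread over 13 to 87%, which nothing in the documents supports.

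Two stronger readings should be resisted. The crude chi-square is not invalid: ignoring centre did not raise the false-positive rate beyond simulation noise. Nor does the omission leave the trial short of its stated 80% power at 180 per arm and a 0.05 level. The point is a minor one of efficiency and interval width. It rests on the assumed 17 unequal centres, normal centre effects and a homogeneous effect on the log-odds scale.

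**What to change.** Make the primary test a Cochran-Mantel-Haenszel test stratified by centre, and report Mantel-Haenszel relative risks with 95% intervals. Use the same method at the interim and final analyses. Fix a rule for merging very small centres before unblinding, and keep the crude chi-square as a supportive analysis. Centre-stratified rank tests for the continuous outcomes are an optional extension.

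The cost is a few sentences in the analysis section and a few lines of code. Centre is known for every child, so no new data are needed. If centres turn out alike, stratifying costs essentially nothing: at SD 0 to 0.3 the two tests agree to within about 0.3 points of power.

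A possible wording is: *The primary outcome will be compared between arms by a Cochran-Mantel-Haenszel test stratified by centre, with Mantel-Haenszel relative risks and 95% confidence intervals; very small centres will be merged by a rule fixed before unblinding.*

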**Dehydration clinical score**

|  | **Normal or mild dehydration**  **(1 Point)** | **Moderate dehydration**  **(2 Points)** | **Severe dehydration**  **(3 Points)** |
| --- | --- | --- | --- |
| Pinch-retraction time | Immediate | Slow (≤2 sec) | Very slow (>2 sec) |
| Feeling of skin to the touch | Normal | Dry | Clammy or cool |
| Condition of buccal mucosa | Moist | Dry | Very dry |
| Tears (if <24 months) | Present | Reduced | None |
| Heart rate | Within normal limits | Mild tachycardia (≤10% above normal) | Moderate tachycardia (>10% above normal) |
| Urine | Normal amount and color | Reduced amount or darker in color | None passed for >6 hr |
| Mental status | Thirsty, alert | Drowsy, irritable, restless | Limp, lethargic |

Severe dehydration defined by:

- children under 24 months of age: score >18

- children 24 months of age of older: score >16

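### The primary comparison is a crude chi-square that leaves out centre and the severity measures assessed before randomisation; adjusting for them is a cheap, probably modest gain in precision

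*Supplement*

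**What the plan says.** The Statistical analysis section of the final protocol is the only analysis text in the documents. For every binary outcome it states: "For categorical outcomes, differences between groups will be evaluated using the chi-square test". It adds: "Relative risks and 95% confidence intervals will be presented for categorical data". It names no covariate, regression model or centre term. Baseline variables appear only in tests comparing the three groups at entry.

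The primary outcome (Outcomes section) is binary: "Percentage of patients needing nasogastric or intravenous rehydration after symptomatic oral treatment failure". The Randomization section stratifies the list by participating centre, in blocks of nine.

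Three possible predictors must be assessed before a child can be randomised:

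- **Age.** The Study Population section limits entry to 1 to 6 years.
- **Vomiting.** The same section requires "more than three episodes of non-bilious, non-bloody vomiting within the previous 24 hours".
- **Dehydration score.** Severe dehydration is an exclusion, defined on the Annex 1 scale with age-specific cut-offs, for example "children 24 months of age of older: score >16". The tears item is scored only under 24 months, so there are seven items (range 7-21) below that age and six (range 6-18) from it.

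The Information retrieval section describes an enrolment questionnaire that covers demographics and history of the present illness. It does not mention a numeric vomiting count or a total score.

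**The concern.** A child's state at entry may well predict whether oral rehydration fails. If it does, a crude comparison leaves that variation in the error term, and the confidence interval is wider than it need be. Leaving out a stratification factor acts in the same direction. If centres differ in how often they give nasogastric or intravenous fluids, stratified randomisation has balanced that difference, but the crude test still counts it as noise.

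The trial has limited power to spare for its smallest planned contrast in power terms, placebo v domperidone. The final protocol also allows for closing short of the target: the second interim analysis falls on the official closing date if the planned number has not been reached. Precision that needs no extra children or visits is worth having in that setting.

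**Working it through.** **Inputs from the Sample size estimates section.** The planned rates are "50% in placebo group to 35% in domperidone group and 20% in ondansetron group", with 180 children per arm, 80% power, and "given a two-sided type I error of 0,05".

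**Step 1. Reproduce the plan's figure (50% v 35%, crude test).**

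n = [1.960·√(2p̄(1−p̄)) + 0.8416·√(p₀(1−p₀)+p₁(1−p₁))]² / (p₀−p₁)², with p̄ = 0.425.

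- First term: 1.960 × √0.48875 = 1.370.
- Second term: 0.8416 × √0.4775 = 0.582.
- n = 1.952² / 0.0225 = 169.3, so 170 per arm. With continuity correction it is 183, within 3% of the planned 180.
- Power at 180 without correction: (0.15×√180 − 1.370)/0.691 = 0.929, or 82.4%. With the correction it is about 79.4%. With an unpooled standard error of √(0.4775/180) = 0.0515, it is 83.0%.

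The plan's figure is thus sound for the crude test. For 35% v 20%, power at 180 per arm is 89.3%. For 50% v 20% it exceeds 99.9%.

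**Step 2. Effect of adjustment.** *Assumption, not in the documents:* one standard-normal baseline predictor X that combines the covariates, with the same log odds ratio in both arms. Let mₖ(X) be the risk in arm k, with its intercept set so that the marginal risks stay at 50% and 35%.

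- Crude variance of the risk difference × n: p₀(1−p₀) + p₁(1−p₁) = 0.4775.
- Adjusted (logistic model, standardised): E[m₀(1−m₀)] + E[m₁(1−m₁)] + ½·Var(m₁−m₀).
- Effective n per arm = 180 / (1 − variance reduction). This goes into the power formula of step 1.

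| Odds ratio per SD (assumed) | Variance reduction | Effective n per arm | Power, 50% v 35% |
|---|---|---|---|
| 1.0 | 0% | 180 | 82.4% |
| 1.25 | about 1% | 182 | 82.8% |
| 1.5 | about 4% | 187 | 83.8% |
| 2.0 | 9-10% | 199 | 85.9% |
| 2.5 | about 15% | 211 | 87.9% |

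**Step 3. Check by simulation** (4,000 trials per setting, 180 per arm, two arms, one covariate; crude chi-square against standardised logistic with robust standard error).

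- Odds ratio 1.0: power 82.3% crude, 82.6% adjusted; no change in variance.
- Odds ratio 1.5: 81.4% and 83.1%; variance down about 3%.
- Odds ratio 2.0: 81.6% and 85.7%; variance down about 8%.
- For 35% v 20%, odds ratio 2.0: 89.4% and 91.6%.
- Type I error with 35% in both arms and odds ratio 2.0: 5.2% crude, 5.4% adjusted.

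The Monte Carlo standard error is about √(0.82×0.18/4000) = 0.6 percentage points. The spread in the crude figures is noise, and the results agree with the table.

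**Step 4. Centre.** The documents give no between-centre variation in the outcome, so no gain from this term can be computed. Unit numbers in the Summary of changes run to 17. If all recruit equally, 540/17 is about 32 children per centre, or about 11 per arm per centre. Some centre terms will therefore be sparse.

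**The case against.** The strongest reply is that nothing is broken. A crude chi-square is valid in a randomised trial, its interval already allows for chance imbalance, and the sample size was built for it. That stands. A reader might infer that the primary result would be biased, or that the trial is underpowered, because baseline severity is left out. The documents support neither reading.

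A reader might also infer that all three predictors are held for every child. Only age is clearly covered, as a demographic item. The vomiting count and the score serve as entry thresholds, which a form could record as yes or no. That numbers exist is an inference from the eligibility checks. This stands and makes the fix conditional.

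The predictors may also be weak. Severe dehydration is excluded, every child has had more than three episodes and has already failed a first oral attempt, and the outcome is triggered by vomiting or refusal at the second attempt. Such selection narrows the covariate range, so strong prognostic value cannot be taken as given and the range must include no gain.

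The check used one covariate and two arms, whereas the proposed model has three arms, several covariates and up to 17 centres. Sparse centres could stop it converging, and missing baseline values could drop children from an intention-to-treat analysis. Both need a stated rule, but neither is a reason to keep the crude test as primary.

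Finally, the stopping levels concern ondansetron, whose crude power is already 89.3% or more, so 50% v 35% is the contrast where extra precision matters most. That is fair. Placebo v domperidone still falls within the stated objective.

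No separate analysis plan is shown, and one might hold supportive adjusted models. The primary test, however, is stated, and it is unadjusted.

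**Conclusion.** The point holds as a worthwhile improvement in efficiency, not as an error. The planned test ignores the stratification factor and pre-randomisation values that eligibility requires to be assessed. For 50% v 35% at 180 per arm, adjustment would cut the variance by between 0% and about 15%. Power would go from about 82-83% to somewhere between no change and about 88%. This rests on an assumed combined odds ratio per SD of 1.0 to 2.5, which the documents neither give nor exclude, and on the values being available as numbers. If the covariates turn out not to be prognostic, almost nothing is lost. A claim of a large or cost-free gain would go beyond what the documents show.

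**What to change.** Before unblinding, and so before the first interim look, amend the Statistical analysis section as follows.

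- **Primary analysis.** An adjusted analysis that targets the marginal relative risk for each pair of arms with its 95% interval, for example logistic regression with standardisation and robust standard errors. This keeps the effect measure the plan already promises.
- **Covariates.** Arm, centre (small centres pooled by a stated rule) and age. If the case report form holds the numbers, add the vomiting count for the previous 24 hours and the dehydration score. Enter the score as the mean per item, because it has seven items under 24 months and six from 24 months.
- **Missing baseline values.** A simple stated imputation, so that every randomised child stays in.
- **Convergence.** A named fallback if the model does not fit.
- **Interim looks.** Apply the same model at the 0.0005 and 0.014 levels.
- **Supportive analysis.** Keep the crude chi-square.

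The cost is protocol or analysis-plan wording, a check of the case report form and a little more analysis work. No extra children or visits are needed.
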